## Abstract

Approximately one-third of cancer survivors report a need for professional help to cope with Fear of Cancer Recurrence (FCR). In the REMOTE trial, we aim to investigate the efficacy of two internet-based mind-body techniques to address this currently unmet medical need. Cancer survivors, screened using the Cancer Worry Scale (CWS), are randomly assigned to one of the three study groups: (1) internet-based emotional freedom techniques (iEFT) (*n* = 113), (2) an active control condition internet-based mindfulness meditation intervention (iMMI) (*n* = 113), or (3) a wait-list control group (WLC) (*n* = 113). The interventions iEFT and iMMI are conducted remotely using Microsoft Teams (Microsoft, Redmond, WA), and participants have access to an online platform via the MyNexuzHealth application (nexuzhealth NV, Hasselt, Belgium). The primary endpoint is the level of FCR. Secondary outcomes are emotional distress and quality of life (QoL). If iEFT and/or iMMI appear to be effective in reducing FCR, they could be readily implemented in clinical practice.

## 1. Background

Recent advances in cancer treatment have substantially increased the number of cancer survivors. In 2022, the number of cancer survivors who were diagnosed in the past five years was estimated to be 53.5 million worldwide [1]. Despite the medical progress, mental well-being and quality of life (QoL) after cancer diagnosis and treatment remain poorly addressed in clinical practice [2].

Fear of Cancer Recurrence (FCR) is one of the most frequent psychological complaints reported by cancer survivors, with a prevalence ranging from 39% to 97% [3]. Research on long-term QoL consistently shows that this fear, worry, or concern about cancer returning or progressing is persistent and does not decline with time, although this might be expected [4,5,6,7]. Depending on its severity, FCR can profoundly impact both health and QoL [8].

Approximately one-third of cancer survivors report a need for professional help to cope with FCR [9,10,11]. Although the number of randomised controlled trials (RCTs) investigating FCR is increasing, evidence regarding the effectiveness of these interventions remains limited [9]. At present, there is no widely adopted, evidence-based approach to managing FCR.

The latest theoretical framework for FCR emphasises its multidimensional nature and underscores the role of cognitive processing and metacognition in the development and persistence of FCR [12]. According to this model, improving awareness of thoughts may be a therapeutic approach to alleviate worrisome and unhelpful thoughts that drive FCR [12]. This focus on cognitive awareness is a fundamental component of both Emotional Freedom Techniques (EFT) and mindfulness-based interventions (MBIs) [13,14].

Clinical EFT integrates elements from Cognitive Behavioural Therapy (CBT) and Prolonged Exposure therapy (PE) [15]. These include awareness building, imaginal exposure, cognitive reframing, pre-framing, and systematic desensitisation [15]. To this psychological component, the somatic component of acupressure or “tapping” is added. A meta-analysis by Church et al. demonstrated that integrating acupressure with established psychological interventions significantly enhances the overall therapeutic efficacy of EFT [16].

Mindfulness meditation involves cultivating moment-to-moment awareness of internal and external experiences with an accepting and open attitude [17]. Its beneficial effects on psychological well-being are well established [18]. A recent RCT illustrated the effectiveness of a mindfulness meditation intervention (MMI) to reduce anxiety and depression symptoms in breast cancer patients, which supports our choice for this method as an active control [19,20,21].

In the REMOTE trial (acronym derived from feaR rEcurrecce eMotional freedOm Techniques mindfulnEss), endorsed by the Belgian Society of Medical Oncology (BSMO) Cancer Survivorship Task Force and Belgian Gynaecological Oncology Group (BGOG; BGOG-Gyn1b), we opted for a tele-health or internet-based (i) approach to deliver the interventions: iEFT and iMMI. Online interventions offer greater accessibility, allowing individuals to engage at any time, in their own environment, with the option to remain anonymous. Consequently, tele-health has been established as a viable and effective modality [22,23,24]. Additionally, it holds significant potential to enhance patient empowerment.

This patient-centred, multicentre, pragmatic randomised controlled trial (RCT) aims to compare the efficacy of iEFT, the experimental intervention, and iMMI, the active control, with usual care (a waitlist), as an intervention to reduce FCR in cancer survivors. If proven to be efficacious to reduce FCR, iEFT and/or iMMI could be easily implemented in clinical practice.

## 2. Methods/Design

### 2.1. Aim and Objectives

The primary aim of this study is to examine whether two different interventions (iEFT and iMMI) can improve FCR experienced by cancer survivors, compared to a usual care wait-list control (WLC) group. To translate a statistically significant effect on FCR into a clinically significant change, we would need to detect a between-group difference in mean FCRI at T1 of 10 points (with T1 6 weeks after participation in the iEFT or iMMI programme, or 6 weeks waiting list; see Figure 1).

The secondary and tertiary objectives are listed in Table 1.

Our hypotheses are:iEFT improves FCR compared to the WLC group at T1iMMI (active control intervention) improves FCR compared to the WLC group at T1

### 2.2. Design

We designed a pragmatic multicentre RCT with three study arms and stratified random allocation. Participants in the WLC group receive care from the treatment centre as usual, and participants in the intervention groups also have access to the usual care in addition to participating in the 6-week iEFT or iMMI programme. Although both interventions require patient engagement, the “live attendance” is organised differently: the intervention format of the iMMI programme includes six weekly 2-h sessions, while the duration of the three individually guided iEFT sessions varies. A first iEFT session lasts about 90 min, the second 45 min, and a third 25 min. Time toxicity is included as one of the objectives (i.e., time spent per patient). The study evaluation will be done by comparing the within-group and between-group differences. The potential effect will be assessed over time on a series of patient-reported outcome measures (PROMs). Measurements will take place at baseline (T0; before randomisation), 6 weeks (T1; 6 weeks after T0 for the WLC and 6 weeks after the first iEFT or iMMI session for the intervention groups); 12 weeks (T2; 12 weeks after T0 for the WLC and 12 weeks after the first iEFT or 6 weeks after the last iMMI session for the intervention groups); 24 weeks (T3; 24 weeks after T0 for the WLC and 12 weeks after the last iEFT or iMMI session for the intervention groups). Participants are allowed to withdraw at any time. There will be no follow-up assessments of these drop-outs. The development of the study protocol followed the SPIRIT (Standard Protocol Items: Recommendations for Interventional Trials) guidelines [25]. The planned flow diagram of the REMOTE trial is presented in Figure 1. The protocol is reported according to the SPIRIT guidelines (Supplementary Materials Section SA: Table S1).

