### 2.9. Analysis Plan

Primary outcome measures:The difference in mean scores from the baseline on the FCRI between the iEFT group and the WLC group at T1;The difference in mean scores from the baseline on the FCRI between the iMMI group and the WLC group at T1;

Secondary outcomes measures:Changes in emotional distress, QoL, and health status;The difference in mean scores from the baseline on the FCRI between the iMMI group and the WLC group;

Tertiary outcomes measures:Changes in the cortisol biomarker

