### 2.10. Data Analysis

All planned analyses will be performed according to the intention-to-treat principle.

Descriptive statistics will be used to describe demographic and clinical characteristics.

Clinical and psychosocial outcomes will be compared between groups using linear mixed models. Linear mixed-effects models will assess whether the improvement in FCRI scores and secondary PROMs is significantly different over time. Models will explore time x group as an interaction effect and will include the stratification variables (age, chemotherapy, and gender). Estimated marginal means with 95% confidence interval (CI) will be calculated for each time point for both groups. A 5% significance level will be used.

Within-group differences will be calculated by pairwise comparisons, enabling us to detect differences over time within the three groups. Between-group differences in the primary outcome at the primary endpoint T1 will be further examined with pairwise comparisons with T0 as the reference time point. These analyses will be repeated for the secondary PROMS: distress, QoL, and health status.

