## 3. Results

The initiation visits for the REMOTE study took place between September and December 2024 in all twelve participating centres. The first patient was randomised on 16 October 2024. The number of participants currently stands at 82 of the target 339 on 31 July 2025.

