**Medical data ^2^**				
**PROMs ^3^**				
Fear of Cancer Recurrence Inventory ^4^	X	X	X	X
Distress thermometer	X	X	X	X
38-item Problem List	X	X	X	X
EORTC QLQ-SURV100 ^5^	X	X	X	X
EuroQol EQ-5D-5L	X	X	X	X
**Biomarker cortisol** *	X	X		

Abbreviations: PROMs: Patient Reported Outcomes Measures; EORTC: European Organisation for Research and Treatment of Cancer; QLQ: Quality of Life Questionnaire; SURV100: survivorship questionnaire with 100 items; EuroQol: European Quality of Life. ^1^ T0: baseline (i.e., before randomisation); T1: 6 weeks after start of the iEFT or iMMI programme or 6 weeks after randomisation to the wait-list; T2: 6 weeks after end of the iEFT or iMMI programme or 12 weeks after randomisation to the wait-list; T3: 24 weeks after start of the iEFT or iMMI programme or 24 weeks after randomisation to the wait-list. ^2^ Details can be found in Supplementary Materials Section SC. ^3^ Details can be found in Supplementary Materials Section SD. ^4^ Details can be found in Appendix C. ^5^ Additionally, item 13, 14, 15, 16 and 17 of the EORTC QLQ-C30 have been added. * Optional, needs to be indicated in the Informed Consent Form (ICF).

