	Check-in, sitting meditation with attention for thoughts, discuss home practices, teaching: thoughts are no facts, automatic negative thoughts, personal evaluation of the training and exercise plan, closing meditation and check-out	

* As stated in 2.7, the iMMI programme contains 6 group sessions of 2 h while the iEFT programme includes three individually guided sessions that may differ in time.

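### T1 is timed from T0 or randomisation in the wait-list but from the first session in iEFT and iMMI, so the primary comparison has arm-dependent follow-up and never-starters have no defined T1 date

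*Protocol article*

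**What the plan says.** The protocol article defines T1 in three places.

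- Section 2.2 (Design): "6 weeks (T1; 6 weeks after T0 for the WLC and 6 weeks after the first iEFT or iMMI session for the intervention groups".
- Table 3, footnote 1: "T1: 6 weeks after start of the iEFT or iMMI programme or 6 weeks after randomisation to the wait-list".
- Section 2.1 (Aim and Objectives): "with T1 6 weeks after participation in the iEFT or iMMI programme, or 6 weeks waiting list".

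Baseline is common to all arms: "Measurements will take place at baseline (T0; before randomisation". Section 2.9 defines the first primary outcome as "The difference in mean scores from the baseline on the FCRI between the iEFT group and the WLC group at T1", with a matching one for iMMI. Section 2.10 states: "All planned analyses will be performed according to the intention-to-treat principle". Section 2.2 adds that participants who withdraw are not assessed further.

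The two programmes are delivered differently (Appendix B footnote): "the iMMI programme contains 6 group sessions of 2 h while the iEFT programme includes three individually guided sessions". On accrual, section 3 reports: "The number of participants currently stands at 82 of the target 339 on 31 July 2025". The first randomisation was on 16 October 2024 (section 3), and recruitment is projected to end in March 2027 (section 6).

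**The concern.** A change-from-baseline comparison between randomised arms assumes that the arms are measured the same time after baseline. Here the wait-list clock starts at T0 or randomisation, while the iEFT and iMMI clocks start at the first session. The active arms have extra elapsed time equal to the delay before that session. The article neither states nor limits this delay. Section 2.4 places a coordinator's telephone call after allocation, so the delay is not zero by design.

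Two things are at stake. First, entry requires a CWS score of 10 or more, so some later fall without treatment is plausible. Any fall during the extra weeks would be credited to the intervention. The delay may also differ between individually booked iEFT and group-based iMMI, which would affect the secondary comparison of the two. Second, a T1 date that depends on a first session does not exist for a participant who never has one, whereas every wait-list participant has a T1 date. Missing primary data would then depend on arm and on attendance, which an intention-to-treat analysis is meant to avoid.

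**Working it through.** **1. The definitions side by side**

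| Item | Section 2.1 | Section 2.2 | Table 3 footnote |
|---|---|---|---|
| T1, wait-list | 6 weeks of waiting | T0 + 6 weeks | randomisation + 6 weeks |
| T1, active arms | 6 weeks after participation | first session + 6 weeks | programme start + 6 weeks |
| T3, active arms | not given | last session + 12 weeks | programme start + 24 weeks |

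The T3 entries cannot both hold for iMMI. The sixth weekly session falls 5 weeks after the first, so section 2.2 puts T3 at 5 + 12 = 17 weeks after the first session, against 24 in Table 3.

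**2. Interval from T0 to T1**

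Wait-list: 6 weeks. Active arms: 6 + w weeks, where w is the lag from T0 to the first session. For assumed w = 1, 2, 4 and 6, the interval is 7, 8, 10 and 12 weeks, or 1.17, 1.33, 1.67 and 2.00 times the wait-list interval.

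**3. The plan's own sample size (section 2.5)**

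Inputs: difference 10, SD 27.9, two-sided alpha 0.025, power 0.80. The normal formula gives 148 per arm, or 444 in total, as stated. The t-based figure is 149.2, rounded up to 150 per arm. Multiplied by 1 − 0.6² = 0.64, this is 96 per arm, or 288. Then 288/0.85 = 338.8, or 339. The arithmetic is sound and this point does not change it. For use below: residual SD = 27.9 × √0.64 = 22.32, SE = 22.32 × √(2/96) = 3.22, and power at 96 per arm is 0.806.

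**4. Illustrative iMMI wait**

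Assumptions not in the documents: groups of 6 to 10, filled only from the iMMI arm, starting when the last member joins. The mean wait is then (n − 1)/2 arrival intervals.

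- Observed pace: 16 October 2024 to 31 July 2025 is 288 days, or 41.1 weeks. With 82/3 = 27.3 participants per arm, there is one arrival per arm every 1.505 weeks. Mean wait: 2.5 × 1.505 = 3.8 weeks (n = 6) to 4.5 × 1.505 = 6.8 weeks (n = 10).
- Pace needed for March 2027: 339 − 82 = 257 in about 20 months (86.9 weeks). With 257/3 = 85.7 per arm, there is one arrival every 1.014 weeks. Mean wait: 2.5 to 4.6 weeks.

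**5. Illustrative bias**

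Bias = weekly untreated fall × w. With an assumed fall of 0.2 to 0.5 FCRI points per week:

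- iMMI: from 0.2 × 2.5 = 0.5 to 0.5 × 6.8 = 3.4 points.
- iEFT, with an assumed booking lag of 1 to 2 weeks: from 0.2 × 1 = 0.2 to 0.5 × 2 = 1.0 point.
- No drift: zero.

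With SE 3.22, a spurious difference of 0.5, 1, 2 or 3 points raises the per-comparison two-sided error from 0.025 to 0.027, 0.032, 0.055 or 0.096.

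**6. Never-starters**

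Assumed 5%, 10% or 20% of an active arm, beyond the planned 15% drop-out.

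| Never start | Measured at T1, no benefit: effect | Power | No T1 value: power |
|---|---|---|---|
| 5% | 10 × 0.95 = 9.5 | 0.760 | 0.795 |
| 10% | 10 × 0.90 = 9.0 | 0.710 | 0.782 |
| 20% | 10 × 0.80 = 8.0 | 0.596 | 0.754 |

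The last column keeps the 10-point effect and loses only numbers. Losing never-starters therefore also removes the dilution that an intention-to-treat estimate should carry.

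**The case against.** The case for a small problem is substantial.

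- Section 1 describes FCR as persistent and not declining with time. Regression to the mean after selection would appear largely at the first re-measurement, which every arm has, and selection is on the CWS rather than the FCRI. This stands: a steady weekly drift is an assumption.
- A reader might infer from the accrual figures that iMMI groups fill slowly and that T1 slips by months. The documents do not support this. They give no group size, do not say that a group must fill before starting, and do not exclude mixed groups: section 2.7.3 lets wait-list participants choose iMMI after T2. The observed pace also includes site initiation, which ran to December 2024.
- Nothing suggests a long lag for iEFT, whose sessions are individual.
- A reader might infer that the article excludes never-starters and so contradicts its intention-to-treat statement. It does not say so. The no-follow-up rule concerns withdrawals, programme start in Table 3 could mean a scheduled date, section 4 has the coordinator following up everyone's questionnaires, and a mixed model can keep the T0 value. What remains is that section 2.2, read as written, gives these participants no T1 date, and a model cannot supply an observation that was never collected.
- The wait-list is untreated and measured at 6 and 12 weeks, so drift over much of the relevant range can be estimated. This stands and is used in the fix.

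The unequal anchor itself is not answered. It appears in both section 2.2 and Table 3.

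**Conclusion.** The point holds as a defect in the schedule, not as a demonstrated bias. Following section 2.2 as written gives an arm-dependent interval for the primary change score and leaves T1 undefined for active-arm participants who never attend. The conflicts over T1, the wait-list anchor and T3 need no assumption.

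The size of any bias cannot be computed from the documents. The range of about 0.5 to 3.4 points for iMMI, or 5% to 34% of the 10-point target, rests on assumed group size, filling rule and drift. The iEFT figure is smaller, and both are zero without drift. It would go too far to conclude that the primary comparison is invalid or that a positive result would be an artefact of timing. This should be fixed, and soon: at the reported count 257 of 339 participants (76%) were still to be enrolled.

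**What to change.** 1. Give every randomised participant a T1 date that does not depend on attendance, for example from a programme start date scheduled at randomisation. Collect T1 from never-starters unless they withdraw from assessment.
2. Record the lag from T0 to first session and the actual date of each questionnaire.
3. Pre-specify a sensitivity analysis of the primary mixed model with actual weeks since T0, using the wait-list values at 6 and 12 weeks to estimate untreated drift.
4. For those still to enrol, preferably use one nominal interval from randomisation in all arms. A single wait-list index date would not be enough, because it cannot match two active arms with different lags.
5. Reconcile sections 2.1 and 2.2 and Table 3 on T1, on the wait-list anchor (T0 or randomisation) and on T3 (12 weeks after the last session or 24 weeks after start).

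Cost: an amendment to the assessment schedule and extra date fields. The sample size stays at 339. With a fixed interval from randomisation, late starters would be measured sooner after their first session, so the sponsor has to choose the interval with that in view. If any wait-list assessment moves later, the sponsor must reconcile it with the programme offer in section 2.7.3. Participants already enrolled keep their dates and are covered by item 3.

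### T3 for the intervention arms falls at about week 17-18 under section 2.2 but at week 24 under Table 3; the T1 wording in section 2.1 also needs tidying

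*Protocol article*

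**What the plan says.** Section 2.2 (Design) and Table 3, footnote 1, each set out the assessment schedule.

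- **T3, section 2.2:** "24 weeks (T3; 24 weeks after T0 for the WLC and 12 weeks after the last iEFT or iMMI session for the intervention groups".
- **T3, Table 3, footnote 1:** "T3: 24 weeks after start of the iEFT or iMMI programme or 24 weeks after randomisation to the wait-list".
- **Programme length, section 2.2:** intervention participants have usual care in addition to "participating in the 6-week iEFT or iMMI programme". The same section gives iMMI as six weekly sessions and iEFT as three sessions, with no spacing stated for the three.
- **T2, section 2.2:** "12 weeks after the first iEFT or 6 weeks after the last iMMI session for the intervention groups". **Table 3:** "T2: 6 weeks after end of the iEFT or iMMI programme or 12 weeks after randomisation to the wait-list".
- **T1, section 2.2:** "6 weeks after T0 for the WLC and 6 weeks after the first iEFT or iMMI session for the intervention groups". **Table 3:** "T1: 6 weeks after start of the iEFT or iMMI programme or 6 weeks after randomisation to the wait-list". **Section 2.1 (Aim and Objectives):** "with T1 6 weeks after participation in the iEFT or iMMI programme, or 6 weeks waiting list".

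Section 2.10 (Data Analysis) fits linear mixed models with a time-by-group interaction and reports estimated marginal means at each time point. It names T1 as the primary endpoint. Section 2.7.3 lets wait-list participants take up either programme once T2 is complete.

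**The concern.** The clause that defines T3 in section 2.2 carries a 24-week label, but its rule for the intervention arms does not lead to week 24 when the programme lasts 6 weeks. Table 3 gives a different rule, which does.

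If section 2.2 is followed, one T3 level of the mixed model combines intervention data from about week 17-18 with wait-list data from week 24. The interval from T2 to T3 is then about 6 weeks in the intervention arms and 12 weeks in the wait-list. A durability result reported as 24 weeks would really describe 17-18 weeks. If Table 3 is followed, the label is right and section 2.2 misdescribes the data.

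The trial has twelve sites and was recruiting when the article was written: section 3 reports 82 of 339 participants on 31 July 2025. The first patient was randomised on 16 October 2024, and 24 weeks from that date is early April 2025, so some T3 questionnaires may already have been answered. An assessment taken in the wrong week cannot be repeated.

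A lesser matter is the T1 phrase in section 2.1. Taken word for word, it counts 6 weeks from the end of participation rather than from the start. T1 is the primary time point, so its wording should be the same everywhere.

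**Working it through.** All weeks are counted from the first session.

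**Inputs**

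- Programme length: 6 weeks, both programmes (section 2.2).
- iMMI: six weekly sessions (section 2.2), so five intervals between first and last. The last session is at week 5, or week 6 if the end of the programme is used.
- iEFT: three sessions, spacing not stated. The last session is taken to fall by week 6 because the programme is called a 6-week one. The two T2 rules support this: 12 weeks after the first iEFT session (section 2.2) and 6 weeks after the end of the programme (Table 3) describe the same visit only if iEFT ends at week 12 − 6 = 6.

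**Step 1. Can the section 2.2 rule give its own label of 24 weeks?**

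T3 = last session + 12. Setting T3 = 24 requires the last session at week 24 − 12 = 12. That is twice the stated programme length, so the label cannot be reproduced.

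**Step 2. Where does the section 2.2 rule put T3?**

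- Last session at week 5: 5 + 12 = 17.
- Programme end at week 6: 6 + 12 = 18.

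**Step 3. Compare with Table 3.**

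- 24 − 17 = 7 weeks.
- 24 − 18 = 6 weeks.

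| Arm | T3 under section 2.2 | T3 under Table 3 | Gap |
|---|---|---|---|
| iEFT, iMMI | about week 17-18 from first session | week 24 from programme start | 6-7 weeks |
| Wait-list | week 24 from T0 | week 24 from randomisation | none of note |

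**Step 4. Does T2 show the same problem?**

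Section 2.2 gives week 12 for iEFT and 5 + 6 = 11 to 6 + 6 = 12 for iMMI. Table 3 gives about week 12 for both. T2 therefore agrees to within a week, and the contradiction is confined to T3. The T2-to-T3 interval in the intervention arms is about 18 − 12 = 6 weeks under section 2.2 and 24 − 12 = 12 weeks under Table 3.

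**Step 5. T1.**

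Section 2.2 and Table 3 both give week 6. The section 2.1 phrase taken word for word gives 5 + 6 = 11 to 6 + 6 = 12, which is the T2 visit. Both schedules list T1 and T2 as separate assessments, so the word-for-word reading does not fit the rest of the article.

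**Step 6. Sample size.**

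Section 2.5 uses a 10-point difference at T1, a standard deviation of 27.9, 2.5% two-sided significance, 80% power, a correlation of 0.6 and 15% drop-out. The T3 date does not enter, so the figures of 444, 288 and 339 are unaffected.

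**The case against.** The strongest reply is that T3 is not the primary time point. The hypotheses, the primary outcome measures and the sample size all refer to T1. Section 2.2 itself labels T3 as 24 weeks and Table 3 gives 24 weeks for every arm, so the offset from the last session may be one stray clause. This stands as a limit on the consequences. It does not remove the contradiction, because the clause is a working rule for two of the three arms and someone scheduling questionnaires could follow it.

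A second reply is that the T3 comparison with the wait-list is already weak. Wait-list participants may start a programme after T2, so by week 24 they may no longer be untreated. This also stands: unequal timing adds to that limitation and is not the main one. The iEFT-iMMI comparison at T3 uses the same rule in both arms under either definition, so what changes there is how long after the programme durability is judged, not the balance between arms.

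A third reply is that week 17-18 is partly assumed for iEFT. That is right, and it is stated as an assumption above.

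A reader might infer from section 2.1 that the primary endpoint has a 6-week discrepancy, with week 11-12 in the interventions set against week 6 in the wait-list. The documents do not support this. The two passages that set the schedule agree on week 6, and the section 2.1 phrase is a parenthesis in the aims that pairs participation with a 6-week wait. It most plausibly means six weeks of participation, since otherwise T1 and T2 would be the same visit. Figure 1, cited there, is not shown and could not be checked.

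Nor do the documents show that any site or the platform has used conflicting dates. The full operational protocol is not at hand. Visit windows are normally left to the statistical analysis plan, and their absence here is not a defect.

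**Conclusion.** The T3 contradiction is real and numerical. For the intervention arms the two definitions differ by 6-7 weeks: about week 17-18 under section 2.2 and week 24 under Table 3. This is direct arithmetic for iMMI and rests, for iEFT, on the last session falling by week 6. It matters for the T3 estimates in the time-by-group models, both durability within each programme and the contrast with a wait-list measured at week 24 that may by then have been treated. The T1 primary analysis and the sample size are untouched.

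The T1 phrase in section 2.1 is ambiguous and worth correcting because T1 is the primary time point. It is a drafting matter and not a demonstrated error in the primary endpoint.

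The article does not settle which T3 rule is intended, and this review does not choose between them.

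**What to change.** 1. Reconcile section 2.2 and Table 3, footnote 1, to a single T3 definition for the intervention arms, and make the week label agree with it.
2. Confirm from the questionnaire platform which T3 schedule has been applied to participants already enrolled.
3. If anyone was assessed on the other schedule, use actual assessment dates for those participants in the T3 analysis and report how many there were.
4. Align the T1 phrase in section 2.1 with section 2.2 and Table 3, which already agree on 6 weeks from the first session or programme start.

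The cost is a protocol clarification and a check of the platform's scheduling. No additional patients are needed and the sample size does not change. It is best done now, since recruitment is projected to run to March 2027 and most T3 assessments were still to come at the status date in the article.
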